## Abstract

**Objectives:**

Pressurized IntraThoracic Aerosol Chemotherapy (PITAC) is a minimally invasive cancer-directed therapy for patients with malignant pleural effusion (MPE) and/or pleural metastasis (PLM). PITAC is based on Pressurized IntraPeritoneal Aerosol Chemotherapy, which has proven to be safe and feasible. Since 2012, 47 PITACs have been published, and prospective data on feasibility, safety and potential local response are lacking.

**Methods:**

The prospective, controlled, phase-I study is designed to treat MPE with PITAC. There are no data to support the estimated number of patients needed, but previous experience estimates the non-access rate to 20 %. Twenty eligible patients with MPE will receive two or more PITACs at four-week intervals. During video-assisted thoracoscopy, MPE and/or pleural lavage fluid is evacuated, and the extent of visible PLM is assessed. Pleural biopsies are collected, if possible, for histological response as per Thoracic Regression Grading Score (TRGS). Patients are screened for treatment-related intra- and postoperative complications. The primary outcome is the number of patients with Clavien-Dindo ≥3b or Common Terminology Criteria for Adverse Events≥4 within 30 days. Secondary objectives include PLM-score, TRGS and cytology, length of hospitalization, personnel safety, quality of life, and change in MPE volume.

**Results:**

PITAC is expected to be safe and feasible for patients and personnel, and achieve positive results in the reduction of MPE volume.

**Conclusions:**

The results may significantly impact the next clinical, technical, and scientific steps in the implementation of PITAC. Given the suboptimal treatment options for MPE and the seemingly promising results of PITAC, we find the implementation of PITAC ethically reasonable and sound.

## Introduction

When the spread of cancerous cells to the pleural cavity disrupts the equilibrium between absorption and excretion of fluid, the result is malignant pleural effusion (MPE) [1, 2]. Mesothelioma, lymphoma, lung, breast, ovarian, and gastrointestinal cancers are the most frequent causes of MPE [3]. MPE indicates an advanced disease with high mortality, poor quality of life and a life expectancy of 3–12 months [1, 4, 5]. The patients present with progressive shortness of breath, chest pain, cough and weight loss [5]. Recent research has suggested that MPE furthermore promotes tumour growth and chemotherapy resistance [6]. The exact incidence of MPE in Denmark is unknown, but is estimated to approximately 5,000 new cases per year and found equaling 15 % of all cancer patients [5, 7].

The available treatments for symptomatic MPE are suboptimal and with limited influence on patient’s life expectancy as these interventions focus only on relief of symptoms, and 90 % of the patients require repeated interventions [8, 9]. They include intermittent pleural drainage, indwelling pleural catheters, and chemical pleurodesis [5, 10]. Pleurodesis has shown a potential increase in survival suggesting that local treatment of the pleura should be prioritized [11].

Patients with MPE who are in a good general condition and with a remaining life expectancy of more than a few months may have an unmet need for additional treatment, in order to increase their quality of life [9]. Often, these patients have developed loculations, hindering complete drainage of MPE and undergone several different treatments with disappointing results. Hence, new and more effective treatment strategies are needed.

### Pressurized IntraThoracic Aerosol Chemotherapy (PITAC)

The first treatment with PITAC for MPE was performed in Germany in 2012. The concept of PITAC is based on experience from Pressurized IntraPeritoneal Aerosol Chemotherapy (PIPAC) [3]. PIPAC is feasible and safe in the treatment of peritoneal metastasis (PM) 12], [13], [14. In addition, PIPAC directed therapy is repeatable with 4–6 week intervals, and the patients may be discharged at postoperative day 0–1 without significant toxicity [13]. The intraperitoneal nebulization of chemotherapy under high pressure increases distribution and penetration of cytotoxic agents to the peritoneum, which may decrease fluid production 15], [16], [17. Theoretically, it should be possible to achieve the same effects in the intrapleural space when using PITAC, but whether this is feasible, safe and able to provide local response is uncertain [18].

To date, data on 21 patients treated with 38 PITACs have been published worldwide, and at Odense PIPAC Center (OPC), five patients have been treated with 11 PITAC procedures (two non-access). The primary indications were MPE and/or pleural metastasis (PLM) due to malignant mesothelioma, gastric cancer, ovarian cancer, rectal cancer, or breast cancer. A recent review by Hansen et al. suggests that PITAC is feasible, but more prospective data are needed to evaluate patient and personnel safety, and potential local effect [3, 15, 19], [20], [21], [22.

### Aim

This study aims to evaluate patient and personnel safety during the implementation of PITAC in Denmark.

#### Primary and secondary objectives

This is a Phase-I study investigating safety and feasibility of repeated PITAC (minimum of two procedures) in 20 patients. PITAC is considered feasible and safe if four patients or less have severe surgical complications defined as Clavien-Dindo ≥ 3b or life-threatening adverse events (AE) defined as Common Terminology Criteria for Adverse Events v. 6.0 (CTCAE) ≥ 4 within 30 days after the procedure. All medical AEs and surgical complications will be recorded, but only those who are probably or certainly/definitely related to the PITAC directed treatment will provide grounds for assessing the feasibility and safety.

Secondary objectives include (1) macroscopic evaluation of PLM before and after PITAC and evaluation of histological response using a proposed Thoracic Regression Grading Score (TRGS) in biopsies from visible PLM and MPE [23], (2) evaluation of response by pleural lavage fluid (PLF) or MPE cytology, (3) assessment of personnel safety (environmental and biological), and (4) evaluation of the quality of life with EORTC-QLQ-C30 at baseline, day 30 and three months after the last PITAC directed treatment.

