Patients will be excluded from the study if (1) requested by the patient, (2) access to the pleural cavity is not possible due to adhesions or other technical aspects, and/or (3) decline in general health resulting in Eastern Cooperative Oncology Group (ECOG) performance status higher than 2. Following events are considered sufficient reasons for discontinuing a subject from the study (1) withdrawal of consent, (2) death, (3) loss to follow up and/or (4) severe AE or surgical complications. The following information will be recorded for patients who have been excluded from the study: Survival, amount and frequency of MPE drainages and illness specific variables (e.g. CT-scan results).

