### Sample size

There are no data to support the estimated number of patients needed for this phase-I study. The non-access rate, based on previous experience, is estimated to 20 %. This study will include consecutive MPE patients until 20 patients have completed at least two PITAC procedures. Interim analyses will be performed in order to monitor patient safety.

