#### Interim analysis

The reported risk of serious complications during standard thoracoscopy is approximately 5 % [30, 31]. Based on our preliminary experience with PITAC and the limited data from the literature, the risk of adding PITAC to a standard thoracoscopy seems low. However, since the actual risk of PITAC is unknown, we choose to perform an interim safety analysis after every 10 procedures. The study will be discontinued if four or more procedures have led to patients having Clavien-Dindo ≥ 3b or CTCAE≥4 complications/adverse events.

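### A count of exactly four affected patients meets both the success rule and the rule for discontinuing the study

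*Protocol article*

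**What the plan says.** **Success rule** (protocol article, Primary and secondary objectives). The study concerns repeated PITAC in 20 patients. "PITAC is considered feasible and safe if four patients or less have severe surgical complications" of Clavien-Dindo grade 3b or higher, or adverse events of CTCAE grade 4 or higher, "within 30 days after the procedure". The unit is the patient. Relatedness is also required: "only those who are probably or certainly/definitely related to the PITAC directed treatment will provide grounds for assessing the feasibility and safety".

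**Stop rule** (Statistics, Interim analysis). Because the true risk of PITAC is unknown, "we choose to perform an interim safety analysis after every 10 procedures". Then: "The study will be discontinued if four or more procedures have led to patients having Clavien-Dindo ≥ 3b or CTCAE≥4 complications/adverse events". The unit is the procedure. The sentence does not state a relatedness grade or a time window, and does not say whether procedures are counted from the start of the study or within each group of 10.

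**Context.** Sample size: "This study will include consecutive MPE patients until 20 patients have completed at least two PITAC procedures". Study intervention and procedures sets two to three procedures per patient. Recruitment process lists "severe AE or surgical complications" among the sufficient reasons for taking a patient off study.

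**The concern.** Safety is the aim of this study, and these two sentences are the only numerical decision rules that the article gives for it. One calls a count of four acceptable; the other calls it grounds for discontinuing. If four patients are affected, the article supports two opposite statements: that the study reached its limit for harm, and that PITAC was shown to be feasible and safe. Nothing in it ranks one above the other or says what a stopped study may conclude. The choice would then be made after the data are known, at a count that is quite likely to occur.

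**Working it through.** The article gives no derivation of either limit and says that no data support the sample size, so there is no stated figure to reproduce. The check is logical first and then illustrative.

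**Step 1: logic.** Let *k* be the number of affected patients and *j* the number of affected procedures. Each affected patient has at least one affected procedure, so *j* ≥ *k*. With a cumulative count:

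| Affected patients *k* | Success rule (*k* ≤ 4) | Stop limit (*j* ≥ 4) |
|---|---|---|
| 0 to 3 | met | reached only if some patient is affected after more than one procedure |
| exactly 4 | met | reached |
| 5 or more | not met | reached |

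The overlap at four does not depend on the relatedness filter: four patients with related events within 30 days satisfy both sentences. If the count restarts every 10 procedures, the overlap remains when all four fall in one block and no other patient is affected.

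**Step 2: how often both rules are met.**

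Inputs:
- Looks at intervals of 10 procedures (Interim analysis).
- 20 × 2 = 40 to 20 × 3 = 60 procedures (Sample size; Study intervention and procedures).
- Per-procedure risk *p* of 5% and 10%. Both are assumptions: 5% is the article's figure for standard thoracoscopy, not a stated PITAC risk, and 10% is chosen to show a range.

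Further assumptions: procedures are independent, each affected patient has one affected procedure, the count is cumulative, all events are known at the look, and patients who are replaced add no procedures.

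The limit is reached by procedure *N* with probability P(Bin(*N*, *p*) ≥ 4):
- *N* = 40: 13.8% at *p* = 5%, 57.7% at 10%.
- *N* = 60: 35.3% at *p* = 5%, 86.3% at 10%.

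The limit is first reached at look *L* with a count of exactly four with probability

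Σ (a = 0 to 3) P(Bin(*L* − 10, *p*) = a) × P(Bin(10, *p*) = 4 − a).

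At the first look and *p* = 5% this is 210 × 0.05⁴ × 0.95⁶ = 0.10%. All looks:

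| Look at procedure | *p* = 5% | *p* = 10% |
|---|---|---|
| 10 | 0.10% | 1.12% |
| 20 | 1.27% | 8.59% |
| 30 | 3.72% | 14.58% |
| 40 | 6.31% | 14.41% |
| 50 | 8.20% | 10.91% |
| 60 | 9.10% | 7.05% |

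Summing down the columns, and leaving out the final look for the share that is actually halted early:

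| Procedures | *p* | Both rules met | Of all trials, before the final look |
|---|---|---|---|
| 40 | 5% | 11.4% | 5.1% |
| 40 | 10% | 38.7% | 24.3% |
| 60 | 5% | 28.7% | 19.6% |
| 60 | 10% | 56.7% | 49.6% |

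Among trials that reach the limit with 40 procedures, the share with exactly four is 11.4/13.8 = 82% at 5% risk and 38.7/57.7 = 67% at 10%.

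**Step 3: the other reading of the interim count.** If the limit applies within each block of 10, a block reaches it with probability *q* = P(Bin(10, *p*) ≥ 4), which is 0.103% at 5% and 1.28% at 10%. Over four blocks, 1 − (1 − *q*)⁴ gives 0.4% and 5.0%. The conflict is then much rarer, but it is not removed.

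**The case against.** **A monitoring limit and a final criterion serve different purposes and may differ.** This stands in part. A stop limit may be stricter than the final verdict, and a region of five or more that lies inside the stop region is not itself a contradiction. The defect is the count of four, where the two sentences give opposite answers.

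**The success rule is framed for 20 patients with at least two procedures each, so a study stopped at procedure 20 or 30 has not met it.** This is a fair reading, but the rule is stated as a bare count with no minimum denominator and no sentence on stopped studies. The overlap also arises at or near completion, where the denominator is in place.

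**The 39% at 10% risk overstates trials halted for harm and then called safe.** Correct. Of the 38.7 points, 14.4 arise only at the look at procedure 40, when the modelled study is over and nothing is left to stop. The early-stop figure is 24.3%, and 5.1% at 5% risk.

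**The definitions may be closer than they look.** The interim wording is causal, the relatedness sentence could be read as covering interim assessment, and an article may not repeat a time window. This weakens the point about differing definitions but leaves the overlap untouched.

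**A reader might infer that five or more affected patients can never occur without the stop limit being reached.** That needs the cumulative count, which is the natural reading but is not stated. Even then, it does not mean that the study would have stopped first. The count can pass four between looks, or after the last one: with 45 procedures, five or more with no look having triggered occurs in 0.4% of trials at 5% risk and 1.8% at 10%.

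**A reader might also infer that a severe event always ends a patient's participation, so that the two units coincide.** The article calls such an event a sufficient reason, which permits withdrawal but does not require it. One affected procedure per patient is therefore an assumption here.

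**Conclusion.** The decision threshold is wrong as written. Exactly four affected patients satisfy the success rule and, on a cumulative count, always reach the discontinuation limit; on a per-block count they reach it when all four fall in one block. The article does not say which rule prevails. This conclusion rests on the text alone.

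How often it would matter depends on the assumptions shown. On a cumulative count, both rules are met in 11% to 29% of trials at 5% per-procedure risk and in 39% to 57% at 10%, for 40 to 60 procedures. Before the final look the ranges are 5% to 20% and 24% to 50% of all trials. On a per-block count the frequency is far lower.

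The difference in unit and the unstated relatedness grade, time window and counting basis of the interim rule are secondary, but they should be settled in the same edit. The documents do not support the broader claim that the two rules are incompatible over their whole range.

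**What to change.** Reconcile the objectives and interim analysis sections:

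- Set the two limits so that no count satisfies both. Either the success limit lies below the stop limit as now written, or the stop limit lies above the success limit as now written. The sponsor chooses which one moves.
- State that a study which reaches the stop limit, at an interim look or at the end, cannot be declared feasible and safe.
- Use one unit, one relatedness definition and one 30-day window in both rules.
- State whether the interim count is cumulative or restarts with each 10 procedures.

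The cost is one or two sentences in the protocol and possibly a slightly less favourable success limit. No extra patients or data are needed.

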**Figure 1: j_pp-2024-0014_fig_001:**
[figure not shown]
Study flow chart ^a^if visible PLM; ^b^if less than 150 mL of MPE present. AEs: adverse events; FEV1: forced expired volume in the first second; MDT: multidisciplinary tumour; MPE: malignant pleural effusion; PITAC: pressurized intrathoracic aerosol chemotherapy; PLF: pleural lavage fluid; PLM: pleural metastasis; SAT: saturation; TRGS: thoracic regression grading score; VAS: visual analogue score.

Patients may have a pleurocentesis up to 14 days before the planned PITAC directed treatment. In case the patients require drainage of MPE between PITACs, this is possible as an outpatient procedure and registered to ensure that the accumulative amount of MPE from the first PITAC directed treatment can be calculated. Patients may receive treatment with systemic chemotherapy or immunotherapy up to 14 days before PITAC treatment, and antihormonal, tyrosine kinase inhibitor (TKI) and/or steroid treatment may be given continuously. The wash out period from PITAC to systemic chemotherapy or immunotherapy is one week.

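### The 'feasible and safe' verdict leaves out severe events rated only possibly related, discriminates poorly at four of 20 patients, and collides with the interim stopping rule

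*Protocol article*

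**What the plan says.** Under Primary and secondary objectives, the protocol article describes the study thus: "This is a Phase-I study investigating safety and feasibility of repeated PITAC (minimum of two procedures) in 20 patients". The success criterion follows: "PITAC is considered feasible and safe if four patients or less have severe surgical complications defined as Clavien-Dindo ≥ 3b", or a CTCAE grade 4 or higher event, "within 30 days after the procedure". All events are recorded, but "only those who are probably or certainly/definitely related to the PITAC directed treatment will provide grounds for assessing the feasibility and safety".

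Two other places bear on the same count:

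- **Abstract, Methods.** It begins "The primary outcome is the number of patients with Clavien-Dindo" and names the same grades and the 30-day window. It states no level of relatedness, although the sentence on screening just before it speaks of treatment-related complications.
- **Interim analysis.** Safety is reviewed after every 10 procedures. The study is discontinued once four or more procedures have led to events of these grades. No level of relatedness is given.

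The Interim analysis section gives this background: "The reported risk of serious complications during standard thoracoscopy is approximately 5" %. It explains the interim looks by saying "since the actual risk of PITAC is unknown". Under Study intervention and procedures, the article states: "The wash out period from PITAC to systemic chemotherapy or immunotherapy is one week". The Study design section describes a non-randomized, non-blinded, single-centre study. The Sample size section says that no data support the number of patients, and no unacceptable risk or error rate is given for the cut-off of four.

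**The concern.** A bar of probable or definite relatedness presupposes that the toxicity profile is known well enough to attribute events with confidence. Here the plan says the opposite, and there is no control group to help. Patients have advanced cancer and may receive systemic chemotherapy or immunotherapy up to 14 days before PITAC and again from one week after it. A severe event in weeks two to four can therefore have a competing explanation, and a rating of 'possible' removes it from the verdict. The filter works in one direction only: it can lower the count but never raise it.

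The cut-off itself is a second, separate weakness. If it lets through risks that most readers would not call safe, a positive verdict says little. The article's conclusions section says the results may shape the next clinical steps for PITAC, so a bare statement of safety could carry more weight than 20 patients can support.

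**Working it through.** **No figure to reproduce.** The article gives no error rates, no unacceptable risk and no derivation of 20 or of four. The check is therefore of how the stated rule behaves.

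**Inputs.** n = 20 patients and success at ≤4 affected patients (Primary and secondary objectives); two to three procedures per patient (Study intervention and procedures); looks every 10 procedures and discontinuation at ≥4 event procedures (Interim analysis); about 5% serious complications in standard thoracoscopy (Interim analysis).

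**Step 1: the worst result still accepted.** Four of 20 is 20%. The Clopper-Pearson 95% limits are Beta(0.025; 4, 17) = 5.7% and Beta(0.975; 5, 16) = 43.7%.

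**Step 2: chance of passing on the success criterion alone.** P(X ≤ 4) with X ~ Binomial(20, p), where p is the true per-patient risk of a counted event:

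| p | P(X ≤ 4) |
|---|---|
| 5% | 99.7% |
| 10% | 95.7% |
| 15% | 83.0% |
| 20% | 63.0% |
| 25% | 41.5% |
| 30% | 23.8% |
| 40% | 5.1% |

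The chance falls to one half only at a risk of about 23%, and to 5% only at about 40%.

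**Step 3: adding the interim rule.** Let r = 1 − (1 − p)^(1/k) be the per-procedure risk for k procedures per patient. Assumptions: independent procedures, patients treated one after another, no discontinuation after an event, and the same events counted by both rules. The chance of not being stopped and having at most four affected patients (200,000 simulated runs; ranges cover k = 2 and 3) is:

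| p | Look at the last procedure | No look at the last procedure |
|---|---|---|
| 15% | 61–62% | 72–76% |
| 20% | 37–38% | 49–54% |
| 25% | 19–20% | 29–33% |

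The middle column can be checked exactly. With a look at the last procedure, not stopping means at most three event procedures overall. For k = 2 and p = 20%, r = 1 − √0.8 = 10.56% and P(Binomial(40, r) ≤ 3) = 37.9%. For k = 3, r = 7.17% and P(Binomial(60, r) ≤ 3) = 36.8%.

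**Step 4: scale.** If the 5% thoracoscopy figure is per procedure, the per-patient equivalent is 1 − 0.95² = 9.8% for two procedures and 1 − 0.95³ = 14.3% for three. A per-patient risk of 20% is then 20/14.3 = 1.4 to 20/9.8 = 2.0 times that figure.

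**Step 5: the two rules side by side.** Suppose four patients each have one event procedure, and all four events are rated definitely related. Four patients is within the success limit. Four event procedures is also the point at which the study is discontinued. The rules differ in unit (patients against procedures), and only one states a relatedness bar.

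**The case against.** Relatedness filters are common in early-phase trials. These patients have a life expectancy of 3 to 12 months, so a count of every severe event would mix disease with treatment. All events are recorded in any case. This stands as a reason to filter, but not as a reason to exclude 'possible' events when the risk is unknown.

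The stopping rule also removes part of the leniency seen in Step 2. That stands too, and it is why both sets of figures are given.

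Several stronger readings are tempting, and the documents do not support them:

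- **That the abstract and the interim rule count events from any cause.** The abstract screens for treatment-related complications, and the interim wording is causal. What is unstated is the level of relatedness.
- **That the investigators who treat the patients decide relatedness.** The article does not say who judges it.
- **That a definite share of severe events would be lost to the filter, and that the chance of passing rises by a known amount.** The documents give no such share. Any figure would also depend on whether the interim rule applies the same filter.
- **That the upper limit should be held against 5%.** That figure describes thoracoscopy without the same grading, and appears to be per procedure. With 20 patients, even no events gives an upper 95% limit of 16.8%, so no result could meet it.

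**Conclusion.** The point holds in two linked parts. First, the verdict excludes severe events rated only possibly related in a setting where that rating will be hard to avoid. The direction of the effect is certain, because the count can only fall; its size cannot be derived from the documents. Second, the rule separates acceptable from unacceptable risk poorly. A true per-patient risk of 20% is called safe with probability 63% on the success criterion alone, or about 37–54% with the interim rule. At 25% the figures are 41% and about 19–33%. The ranges with the interim rule rest on independent procedures, sequential treatment and no discontinuation after an event. The exact binomial figures need only independent patients with a common risk.

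The success and discontinuation criteria also contradict each other at four event procedures in four patients. These passages must be reconciled; which should give way is not settled here.

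**What to change.** 1. Make the primary count the number of patients with a qualifying severe event at least possibly related to PITAC. Show the probable-or-definite count and the all-cause count as supporting tables.
2. State one relatedness rule, in the same words, in the abstract, under Primary and secondary objectives, and under Interim analysis.
3. Reconcile the success threshold with the discontinuation threshold, including the unit (patients or procedures), so that no result can satisfy both.
4. Report the per-patient proportion with its exact 95% interval, and word the conclusion by the upper limit instead of a bare 'safe'.

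The change is to wording and tables. It needs no further patients and no new data, since the present filter already requires relatedness to be recorded. The downside is that some events due to the disease or to systemic therapy will be counted, so the headline rate will look less favourable. The supporting tables let a reader see how much of it that explains.
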